### **ANALYSIS:**

The following comparisons will be made **(1)** MELAS sibs will be compared to themselves both on L-arginine (single oral dose and 6 wk steady state trial) vs. off L-arginine (pre-trial baseline) to evaluate effects of treatment. **(2)** They will be seen post L-arginine therapy to determine if there are lasting effects up to 8 wks vs. off L-arginine (baseline). **(3)** MELAS sibs at baseline vs. controls **(4)** MELAS sibs on L-arginine (single oral dose and 6 wk steady state trial) vs. controls. Four different end-points will be compared **(A)**  $^{31}\text{P}$ -MRS study of quadriceps for PCr recovery and ATP levels **(B)** maximal oxygen uptake  $\text{VO}_{2\text{max}}$  (ml  $\text{O}_2$ /kg/min) and mean peak work capacity (Watts/kg) **(C1)** CVR to  $\text{CO}_2$  stimulus **(C2)** CVR to neuronal stimulus. Comparisons will be made of the different parameters and to determine whether there are clinically significant differences between the MELAS sib groups (treated vs untreated), and MELAS sib vs control groups (Student's t-test). We understand that the sample size has insufficient power to detect statistically significant differences. However estimates of means and SD's obtained from this pilot study will be used in a future study to determine adequate sample sizes to detect statistically significant differences in these parameters.

**A. P-Magnetic resonance spectroscopy protocol – Muscle function investigation:** We will study exercising quadriceps using our MR-compatible up-down ergometer and our well established aerobic exercise protocol at 65 % of maximal voluntary contraction (25). Testing will be done between 60 to 105 minutes after an oral L-arg dose of 200 mg/kg to ensure maximum serum arg at time of exercise. **Predicted outcome:** Untreated sibs: P-MRS of quadriceps will show a delay in PCr recovery/resynthesis after exercise, reflecting the reduced ATP synthesis rate compared to controls. We predict that the degree of delay in PCr recovery will be directly proportional to the % mutant mtDNA in blood. Following L-arginine, we predict a faster PCr recovery/resynthesis after exercise and increased ATP levels. P-MRS data will be collected on our GE Twin Speed EXCITE™ III 12.0 1.5 Tesla imaging & spectroscopy system at HSC

**B. Maximal Incremental cycle testing to determine total body maximal aerobic capacity:**

Maximal incremental cycle ergometry is conducted in our CardioRespiratory Exercise Lab at HSC by our established protocols (26). Serum CK and quantitative AA (for arginine, ornithine and citrulline) will be measured pre- and post- exercise as well as eNO in order to correlate aerobic exercise parameters with serum arg and eNO levels..Exercise testing will be performed between 60 - 75 min following an oral L-arg dose (200 mg/kg) to ensure maximal serum arg at time of exercise. **Predicted outcome:** Pre-treatment, maximal incremental cycle ergometry will demonstrate a decrease in maximal oxygen uptake  $VO_{2max}$  (ml O2/kg/min) and mean peak work capacity (Watts/kg) which will be directly proportional to % mutant mtDNA (27). We also predict exaggerated circulatory and ventilatory responses to exercise that will increase exponentially in relation to increasing % mutant mtDNA. We anticipate that even though there will be a decrease in O2 uptake by exercising muscle due to defective oxidative phosphorylation, there may be an additional defect, in response to increased exercise demands, related to impaired peripheral vasodilatation, due to endothelial dysfunction of small muscle arterioles. We predict this will respond to L-arg. Alternatively, if aerobic capacity and peak power do not improve with L-arg, this may indicate that endothelium of muscle and heart arterioles is less affected than brain arterioles, given their significantly lower % of mitochondria compared to CNS vessels, and that peripheral vasodilatation is already maximal.

**C. CerebroVascular Reactivity Studies – Functional MRI-Blood oxygen level dependent (BOLD) of brain**

**Measurement of Exhaled Nitric Oxide (eNO) and early morning (first am) NO metabolites:**

All subjects will have their eNO levels measured before and after graded maximal incremental cycle ergometry. We will measure eNO levels to determine the effect of oral L-arginine on NO production in our sibs in order to confirm their ability to synthesize NO from arginine and to correlate the eNO concentrations with serum arginine concentrations. We will also measure NO metabolite concentrations in the first morning urine, as this is an accurate reflection of systemic

Pilot study to investigate the efficacy of L-arginine therapy on endothelium-dependent vasodilation & mitochondrial metabolism in MELAS syndrome.

NO production. eNO will be measured using single breath on-line measurements for the assessment of lower airway NO (28,29). Urine NO metabolites will be detected spectrophotometrically by measuring the final stable equimolar degradation products, nitrite and nitrate (NOx) (30).

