## **STUDY PLAN**

Brain BOLD-fMRI allows us to examine CVR non-invasively *in vivo* in 4 MELAS sibs vs 4 age-, sex- and menstrual cycle- matched normal controls. To determine the relative contributions of (a) impaired isolated microvascular endothelial cell function in response to changes in  $\text{PCO}_2$  (using a rebreathing circuit) vs (b) impaired occipital neuronal cell (in response to a strong visual stimulus) activation of CVR, we will study both paradigms using brain BOLD-fMRI. Given the variable severity of neurological phenotypes in this family, we will determine the relationship between the severity of the phenotype and the degree of dysfunction in CVR to  $\text{PCO}_2$  vs neuronal stimulus. This correlation may provide a useful tool for predicting the risks for SLEs. To determine the correlation between brain and muscle dysfunction, we will compare brain BOLD-fMRI findings with parameters of total body and muscle oxidative function as determined by maximal incremental cycle ergometry and  $^{31}\text{P}$ -MRS of exercising muscle, respectively. Following these baseline studies, we will then quantify the effect, in only our MELAS sibs, of L-arginine (single oral dose & 6 wk steady state trial) on CVR, neuronal activation, and total body and muscle oxidative function to determine which function(s) is improved. Absorption and exhaled NO production and urine NOx will be measured.

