### **STUDY DESIGN:**

MELAS sibs will participate in 4 test periods. Controls will be tested at baseline once only with no L-arginine (see Table 1 for Timetable of studies)

(1) **At baseline**, both untreated controls and MELAS siblings will undergo clinical and neurological exams and three sets of tests including (A) quadriceps muscle aerobic cycle ergometry in the magnet using P-MRS with pre- and post- CKs to assess degree of muscle effort and plasma quantitative AA to determine any effect of exercise alone on AA profile, (B) maximal incremental cycle test to investigate overall maximal aerobic capacity with pre- and post- serum CKs and lactates and urine lactate/creatinine ratios to assess degree of effort, and serum quantitative AA and exhaled NO (eNO) to determine any effect of exercise alone on these parameters, and (C) BOLD-fMRI of brain to evaluate CVR with pre- and post- AA to establish a baseline. MELAS sibs and controls will have early morning urine NOx metabolites (nitrites, nitrates) measured to establish their baselines. Plasma AA are measured by our certified HSC Core Lab. As estrogen vasodilates cerebral microvessels by increasing endothelial NOS thus increasing NO (20), we will measure CVR at 0, 4 and 12 wks to coincide with the same phase of menstrual cycle in each of 3 menstruating female sibs and serum estradiol levels will be measured in each subject and their respective age-,menstrual cycle matched controls (21).

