(2) **Single Oral L-Arginine Dose Trial:** Four wks after this baseline testing, the MELAS sibs will undergo a trial with a single oral dose of L-arg of 200 mg/kg and will then be retested with the three sets of tests described above. This will allow evaluation of the acute clinical response to a single dose of L-arg and to determine any impact on (a) muscle oxidative function, (b) total body maximal aerobic capacity and (c) CVR. This will also provide an opportunity to evaluate toleration of the dose and any side effects. Tests will be performed at fixed time intervals 60 mins after the oral dose of 200 mg/kg for each MELAS patient to ensure maximum serum L-arg at the time of testing, ending by 2 hrs post-dose. Plasma AA will be measured pre- and post-test procedure to determine the effect of the single oral dose on plasma arg, citrulline and ornithine concentrations as a measure of the efficacy of absorption and to correlate the performance on testing with the concomitant plasma arg concentrations. Following the maximal graded cycle test, (i) exhaled NO (eNO) will be measured to evaluate utilization of L-arg in NO production post oral dose as well as (ii) urinary NO metabolites.

(3) **6 wk Steady State L-Arginine Trial:** If the single oral dose of L-arginine is well tolerated, the MELAS sibs will then be treated with oral L-arginine at 200 mg/kg three times daily (maximum

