### **CONCOMITANT MEDICATION**

There will be no changes to the cofactor/vitamin therapy that the subjects are receiving prior to enrolment in the study.

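### Urinary nitrite plus nitrate is read as systemic NO production, but neither the measurement section nor Table 1 controls or records dietary nitrate before collection

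*Protocol*

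**What the plan says.** The section on exhaled nitric oxide (eNO) and early-morning NO metabolites gives this reason for the urine measure: "We will also measure NO metabolite concentrations in the first morning urine, as this is an accurate reflection of systemic" NO production (the sentence runs across a page break). The metabolites are detected by spectrophotometry, "by measuring the final stable equimolar degradation products, nitrite and nitrate (NOx").

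Study Design, under the single-dose trial, gives the urine measure a role beside exhaled NO after the cycle test: "eNO) will be measured to evaluate utilization of L-arg in NO production post oral dose as well as (ii) urinary NO metabolites".

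Table 1 lists morning urine NOx on Day 1 and Day 2 of Visits 1, 2 and 3 for the siblings, and once at the final assessment after wash-out. Controls have the two mornings of Visit 1 only.

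The treatment comparison is within person. Under Analysis, "MELAS sibs will be compared to themselves both on L-arginine" and off it. Study Design adds: "Controls will be tested at baseline once only with no L-arginine". The groups are "4 MELAS sibs vs 4 age-, sex- and menstrual cycle- matched normal controls".

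The nearest rule on background intake is under Concomitant Medication: "There will be no changes to the cofactor/vitamin therapy that the subjects are receiving prior to enrolment in the study". It does not mention food.

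**The concern.** Nitrate reaches urine from two sources: NO made in the body, and nitrate that was eaten. An assay of total nitrite plus nitrate adds the two together. A first-morning sample can therefore carry the previous day's meals as well as NO production. That eaten nitrate is excreted in urine is general chemistry and is not stated in the protocol.

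If intake differs between the baseline visit and a visit on L-arginine, NOx can rise without any drug effect, or a true rise can be masked. The baseline comparison of siblings with controls is exposed in the same way if the two groups eat differently.

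What is at stake is the reading of mechanism: whether L-arginine raised NO production. The protocol takes care with other influences on NO. It times cerebrovascular testing to the menstrual phase and measures estradiol because estrogen acts through NO. Leaving nitrate intake free in a nitrate assay is out of step with that care. Diet that was neither standardised nor recorded at collection cannot be recovered by any later analysis, so this does not belong to a statistical analysis plan.

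**Working it through.** **1. Is there a figure to reproduce?** No. The protocol gives no NOx standard deviation, effect size, alpha or intake figure. The design argument in step 2 comes first; steps 3 and 4 are illustrations on stated assumptions.

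**2. Which samples can show a drug effect, and what stands beside them?**

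| Visit (siblings) | Morning NOx samples | L-arginine status |
|---|---|---|
| 1, week 0 | Day 1, Day 2 | off |
| 2, week 4 | Day 1 | probably before the dose |
| 2, week 4 | Day 2 | after Day 1 dosing |
| 3, week 12 | Day 1, Day 2 | on, 6 weeks |
| Final assessment, week 20 | one | off |

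At Visit 2 only the Day 2 sample can show a post-dose response, and it follows an evening of uncontrolled eating. The second morning therefore gives no duplicate on-drug value there. Controls have no second visit, so no untreated group shows how NOx moves between visits.

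**3. How far could diet move NOx?** Let E be endogenous nitrate and D dietary nitrate, with equal fractional excretion. Assumed ranges, not from the documents: E = 0.5 to 1.0 mmol/day, D = 0.5 to 2.5 mmol/day.

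- Diet share of NOx, D/(E + D): from 0.5/(1.0 + 0.5) = 33% to 2.5/(0.5 + 2.5) = 83%.
- Full low-to-high change in diet with no drug effect, (E + 2.5)/(E + 0.5): 3.5/1.5 = 2.33 at E = 1.0, and 3.0/1.0 = 3.0 at E = 0.5. A smaller change in diet gives a ratio nearer to 1.
- True 30% rise in endogenous production at constant diet, (1.3E + D)/(E + D): from (0.65 + 2.5)/3.0 = 1.05 to (1.3 + 0.5)/1.5 = 1.20. It shows as 5% to 20%.

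Correcting for creatinine would adjust for urine dilution. It would not remove an eaten load.

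**4. What would that do to a comparison with four siblings?** Assumed: paired t-test, n = 4, 3 degrees of freedom, two-sided alpha 0.05 (critical value 3.182). For a shift of d standard deviations of the paired differences, the noncentrality is d√4 = 2d. The effect that has 80% power is 2.13 SD.

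| Diet shift common to all four (SD) | Rejection rate, no drug effect | Power for the 2.13 SD effect, shift opposed |
|---|---|---|
| 0 | 0.05 | 0.80 |
| 0.5 | 0.111 | 0.595 |
| 1.0 | 0.289 | 0.348 |
| 1.5 | 0.533 | 0.147 |
| 2.0 | 0.755 | 0.054 |

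This table needs a shift common to all four siblings. If diet varies independently between them, with variance equal to the individual variance, there is no systematic shift, but power falls from 0.80 to 0.535.

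**The case against.** Several points on the other side stand.

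- **Exhaled NO leads.** The measurement section gives exhaled NO the task of showing the effect of L-arginine on NO production; urine metabolites are added to it. A reader might infer that the NO evidence rests on urine alone. It does not, although the protocol describes exhaled NO as a lower-airway measure, so it is not a substitute for a systemic one.
- **NOx is not an end-point.** The four under Analysis are muscle spectroscopy, aerobic capacity, and cerebrovascular reactivity to CO2 and to neuronal stimulus. A reader might infer that the treatment findings on these are in doubt. Nothing here touches them.
- **There are repeated and off-drug samples.** Two mornings per visit make a single unusual dinner easier to see at Visits 1 and 3. Weeks 0 and 20, and probably Visit 2 Day 1, show some background variation off drug. This helps, but it does not tell what was eaten before the on-drug samples, and it does not help the one post-dose morning at Visit 2.
- **Shared meals are not documented.** It is tempting to say that one family dinner would shift all four siblings together. The protocol does not say that they eat together or attend on the same dates, and timing by menstrual phase may separate their visits.
- **Low power is admitted.** The protocol says that the sample is too small for significance and is meant to yield means and SDs. That does not excuse a systematic shift, which would pass into those estimates.
- **The copy reviewed is incomplete.** A portion ahead of Study Design is not in it, so the absence of any diet rule in the whole protocol cannot be asserted.

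**Conclusion.** The concern holds as a limited measurement flaw. As written, a diet difference between visits, or between siblings and controls, can imitate or hide a change in urinary NOx, and the plan collects nothing that would reveal it. The unqualified statement that NOx accurately reflects systemic NO production is therefore too strong. The single-dose comparison at Visit 2 is the weakest part, given that the Day 1 first-morning sample probably precedes the dose.

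The size of the bias is not known from the documents. The 2.3- to 3.0-fold and 5% to 20% figures rest on assumed intakes and equal excretion. The rejection rates rest on an assumed test, alpha and common shift. They support the statement that diet can distort the result, not an amount by which it does.

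The consequence is confined to a supporting mechanistic marker. The documents do not support the stronger readings that the four end-points are compromised or that no other NO evidence exists.

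**What to change.** In the measurement section and Table 1:

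- Give siblings and controls the same written low-nitrate diet instructions for the 24 hours before each first-morning NOx sample, with a one-day food record. This covers both mornings of Visits 1 to 3 and the final assessment for siblings, and both mornings of Visit 1 for controls.
- Flag samples taken after a recorded breach and report NOx with and without them. Do not exclude them outright: with four siblings, exclusion could empty the comparison and would add selection after the fact.
- Reword the claim so that first-morning NOx is taken to reflect systemic NO production only when nitrate intake is controlled.

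The cost is an instruction sheet and a short record: seven per sibling (3 visits × 2 mornings + 1) and two per control, so 4 × 7 + 4 × 2 = 36 records in all. The downside is a small burden on participants on the day before each sample.

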**Table 1. Summary Timetable of Clinical Testing**

| Participant Group                        | Clinical Exam and Bloodwork                                                                                       | A.  P-MRS of Exercising Muscle | B. Maximum Graded Aerobic Cycle Test                                                                                                                                                                                                                                                                                                                                              | C. BOLD -fMRI A-15'; B-15'  |
|------------------------------------------|-------------------------------------------------------------------------------------------------------------------|---------------------------------------------|-----------------------------------------------------------------------------------------------------------------------------------------------------------------------------------------------------------------------------------------------------------------------------------------------------------------------------------------------------------------------------------|-----------------------------|
| Visit 1–wk 0                      | Baseline Clinical/Neuro exams                                                                              | Day 1 AM                                    | Day 1 PM                                                                                                                                                                                                                                                                                                                                                                          | Day 2                       |
| 4 Controls baseline only                 | Hb, CK, lactate, estradiol, AA, carnitine T/F, urine OA                                                           | Pre/post CK, AA
AM urine NOx             | Pre/post CK, lactate, AA, eNO, urine L/Cr                                                                                                                                                                                                                                                                                                                                         | Pre/post AA
AM urine NOx |
| 4 MELAS baseline                         | CBC,diff, platelets, lytes, lactate, BUN, Cr, glucose, Ca, PO4, AST, AP, PT, INR, carnitine total/free, estradiol | Pre/post CK, AA
AM Urine NOx             | Pre/post CK, lactate, AA, eNO
urine lactate/creatinine (L/Cr)                                                                                                                                                                                                                                                                                                                  | Pre/post AA
AM urine NOx |
| L-arginine trial                  | Timing of study post-dose                                                                                         | 60-105 min                                  | 60-75 min                                                                                                                                                                                                                                                                                                                                                                         | 75-105 min                  |
| Visit 2–wk 4
Single oral dose | Single Dose Response (60-105 min after oral load)                                                          | Day 1
AM Urine NOx                       | Day 1
PM                                                                                                                                                                                                                                                                                                                                                                       | Day 2
AM Urine NOx       |
| 4 MELAS                                  | Clinical + neurological exam + serum estradiol                                                                    | Pre/post CK, AA                             | Pre/post CK, lactate, AA, eNO, urine L/Cr                                                                                                                                                                                                                                                                                                                                         | Pre/post AA                 |
| START wk 6
L-arg in MELAS     | Questionnaire and clinical exam q 1 wk X 6 by pediatric.                                                          |                                             |                                                                                                                                                                                                                                                                                                                                                                                   |                             |
| Visit 3–wk 12
6 wks ON L-arg  | Steady State Response
clinical + neurological exam                                                      | Day 1
AM Urine NOx                       | Day 1
PM                                                                                                                                                                                                                                                                                                                                                                       | Day 2
AM Urine NOx       |
| 4 MELAS                                  | CBC, diff, platelets, lytes, BUN, Cr, glucose, Ca, PO4, AST, AP, PT, INR, estradiol                               | Pre/post CK, AA                             | Pre/post CK, lactate, AA
eNO, urine L/Cr                                                                                                                                                                                                                                                                                                                                       | Pre/post AA                 |
| STOP L- Arg
-> Wash out    | Questionnaire + clinical exam q 2wk X 4 by pediatrician                                                           | Final assessment

AM Urine NOx        | Key: AA= serum quantitative amino acids to assess arginine, ornithine and citrulline;
CK= serum creatine kinase; OA = organic acids;
eNO= exhaled nitric oxide; NOx = NO metabolites;
BOLD-fMRI: A= CO2 stimulus 15 min; B = visual stimulus 15 min;
Blood samples are taken from a saline lock therefore there will be only ONE venipuncture per day X 2 days |                             |
| Visit 4–wk 20
8wk washout     | Wash-out period
clinical + neurological exam                                                            |                                             |                                                                                                                                                                                                                                                                                                                                                                                   |                             |
| 4 MELAS                                  | CBC, diff, platelets, lytes, BUN, Cr, glucose,Ca, PO4,AA
AST, AP, PT, INR, CK, lactate,                        |                                             |                                                                                                                                                                                                                                                                                                                                                                                   |                             |

